**Fig. 2 Fig2:**
[figure not shown]
SPIRIT schedule of enrollment, interventions, and assessments. Abbreviations: CBT, cognitive behavioral therapy; 1-wk, before or during the first home visit, the equivalent of the baseline of in-home decluttering or waitlist; 4-wk-7wk, assessment points 4 and 7 weeks post-randomization; post, 10 weeks after starting the intervention, the primary endpoint; 3FU-12FU, assessment points 3–12 months after the primary endpoint; HRS-I, Hoarding Rating Scale – Interview; MINI, Mini International Neuropsychiatric Interview; OCD-RD, part from the structured Clinical Interview that assesses all the disorders in the OCD and related disorders; SIHD, Structured Interview for Hoarding Disorder; SI-R, Saving Inventory-Revised; CIR, Clutter Image Rating; ADL-H, Activities of Daily Living for Hoarding; HEI, Home Environment Index; CGI-S, Clinical Global Impression Scale Severity; CGI-I, Clinical Global Impression Scale Improvement; SMURF, Safety Monitoring Uniform Report Form; SCI, Saving Cognitions Inventory; CSQ-8, Client Satisfaction Questionnaire-8; RSI, Relationship between Self and Items; EQ-5D, EuroQol-5D; TiC-P, Trimbos Questionnaire for Costs associated with Psychiatric Illness

#### Primary outcome measures

The primary outcome measures are the self-reported Saving Inventory-Revised (SI-R) [24] and the blind assessor-rated Clutter Image Rating (CIR) [25]. The SI-R is a 23-item questionnaire assessing the severity of hoarding symptoms, including the three subscales difficulty discarding, clutter, and excessive acquisition. Each item is rated from 0 to 4, with a higher number indicating more symptoms of HD; all items are summed to generate a total score. The SI-R is one of the most widely used self-rated measures of HD and has strong psychometric properties and a high discriminant performance [26].

The CIR is a visual scale assessing the levels of clutter in different rooms in the home, using photographs with 9 levels of clutter, and has sound psychometric characteristics [25, 27]. During the in-home decluttering, the social workers will collect the administered measurements. For waitlisted participants, a study assessor will visit the participants’ homes every third week (corresponding to intervention weeks 1, 4, 7, and 10 in the intervention group) in order to complete the pertinent assessment measures. The assessors and the social workers will take photographs of the participants’ homes, which will be rated with the CIR by blind assessors not involved in any parts of the interventions in the trial.

#### Secondary outcome measures

Secondary blinded assessor-rated outcome measures include the Clinical Global Impression Scale (CGI) [28], a brief assessment of the clinician’s view of the patient’s HD severity and improvement. It consists of measures of the severity of illness (CGI-S) and improvement after treatment (CGI-I). Both measures will assess severity and impairment in relation to the HD symptoms only.

Participants will fill out the self-reported version of the CIR [25]. They will also self-rate their cognitions about discarding their possessions using the Saving Cognitions Inventory (SCI) [29] and their level of object attachment by using the visual Relationship between Self and Items (RSI) [30], which is an adaptation of the Inclusion of Other in Self scale [31]. The self-administered EuroQol-5D [32] provides a single index value that will be used in both clinical and economic evaluations of treatment and health care. The Client Satisfaction Questionnaire-8 (CSQ-8) [33] will be used to assess clients’ satisfaction with the in-home decluttering. The Trimbos Questionnaire for Costs associated with Psychiatric Illness (TiC- P) [34] will be used to assess healthcare and societal resource use.

The following secondary measures will be administered as both clinician- and participant-rated outcomes: the Activities of Daily Living for Hoarding (ADL-H) [35], measuring the degree to which hoarding symptoms impair daily functioning, and the Home Environment Index (HEI) [36], measuring the sanitary state of the participant’s homes. Since follow-up assessments will be carried out at the psychiatric clinic, and not in the participant’s homes, the ADL-H and the HEI will solely be administered as self-report forms during these assessment points.

In line with previous studies of HD [37, 38], responder status will be operationalized as clinically significant change on SI-R (change of 14 points or more), and remitter status will be operationalized as being a responder and having a total score of SI-R below a cutoff of 42 [39].

The available relatives/significant persons of the participants will answer questions about demographic variables and will fill out the Family Impact Scale for Hoarding Disorder (FISH) [40], a scale that measures the level of family accommodation to the hoarding behaviors displayed by the relative who hoards and the burden these put on families, and the Caregiver Burden Inventory (CBI), a non-hoarding specific measure [41].

#### Recording and reporting of adverse events

Data on adverse events will be collected using a standardized checklist (Safety Monitoring Uniform Report Form, SMURF [42] at the primary endpoint. If the research team is notified about adverse events at other times, this will be logged, and if needed, an assessment about continued participation in the study will be done. Reported adverse events will be categorized depending on severity and frequency in line with Good Clinical Practice principles. Serious adverse events (i.e., events that result in death, suicide attempt, serious violent incident, or admission to hospital) will be documented and monitored by Karolinska Trial Alliance. If a participant expresses suicidal ideation or a worsening of symptoms is suspected, a clinical assessment including a structured suicide risk evaluation will be conducted and suitable measures will be taken to manage the symptoms.

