### Participants

We will randomize 90 participants to either in-home decluttering or a waitlist. As we expect some participants to drop out from the group CBT prior to randomization, we will recruit participants to CBT until we have randomized 90 of them. We will advertise the trial to clinics and within the social services in Stockholm, patient organizations, and directly to the public via a designated trial website and social media. Participants can either self-refer or be referred to the trial via regular healthcare services.

Potential participants will initially be contacted via telephone by a member of the research team or, in some cases, approached face-to-face at the clinic. The main purpose of this screening is to assess potential eligibility, which includes asking brief questions about hoarding symptoms using the Hoarding Rating Scale – Interview (HRS-I) [13] and each inclusion/exclusion criterion. The inclusion and exclusion criteria are listed in Table 1. If potentially eligible and interested in taking part in the trial, the participants will be booked for a psychiatric assessment, which will be carried out by a psychologist or psychiatrist at the specialist clinic. The aim of this/these visit(s) is to (a) verify that diagnostic criteria for HD (except clutter) are met and (b) quantify the severity of the hoarding symptoms. The Structured Interview for Hoarding Disorder (SIHD) [14] will be administered to assess diagnostic criteria for HD. The Mini International Neuropsychiatric Interview [15] and a short diagnostic interview, the OCD-RD, will be administered to assess psychiatric comorbidities. The OCD-RD is originally based on the Structured Clinical Interview (SCID) for DSM-5 and assesses all the disorders in the OCD and related disorders chapter [16].

**Table 1 Tab1:** Eligibility criteria

**Inclusion criteria**	**Exclusion criteria**

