#### Waitlist

Participants assigned to the waitlist will receive no in-home decluttering for a period of 10 weeks after group CBT. During this period, a study assessor will visit the participants every third week to ask them to complete the pertinent assessment measures and have photographs of the home taken for blinded CIR ratings. Audio from all home visits will be recorded and monitored by supervisors to ensure that no unintended interventions were given during these visits. After these 10 weeks (primary endpoint), participants on the waitlist will be crossed over and offered the same intervention as the active group.

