### Outcome measures

Assessments will be conducted at several time points throughout the trial. All measures and measurement points are shown in Fig. 2; for more details, see supplement 1 (full protocol). Baseline assessment occurs after CBT, and during the first home visit of in-home decluttering or waitlist. Two mid-intervention assessments will be done, one at week 4 and the other at week 7 after randomization. The primary endpoint is 10 weeks after randomization.

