### Ethics and dissemination

The Swedish Ethical Review Authority approved the study (reference numbers 2020-05798 and 2021-06176). From a clinical point of view, the proposed combined interventions pose a small risk to participants. All patients receive a thorough clinical assessment and those with more immediate needs or risks will be offered alternative treatment options. No patients will be denied current standard treatment (i.e., CBT for HD) due to drop-out from the study or if they do not want to enroll at all. Adverse events will be carefully monitored throughout the trial, but the risk of serious adverse events due to the interventions is considered very low. The adverse events that may be experienced in the short term, such as anxiety due to discarding belongings, are difficult to avoid and are often necessary for the participants to reduce their hoarding difficulties in the long run.

We tentatively plan to publish a main paper with the efficacy results and secondary papers with cost-effectiveness results and the naturalistic follow-up data. We also plan to disseminate the results of the research to study participants, the Swedish OCD Foundation (*Svenska OCD-förbundet*), members of the task force, politicians, and the general public. Results will also be presented at scientific conferences.

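### As the article reads, the adverse-event checklist is given at week 10 only, so the waitlist arm is not systematically asked about harms after its own decluttering

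*Protocol article*

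**What the plan says.** The Protocol article, Recording and reporting of adverse events, names one instrument and one time: "Data on adverse events will be collected using a standardized checklist (Safety Monitoring Uniform Report Form, SMURF [42] at the primary endpoint". For all other times it gives a passive rule: "If the research team is notified about adverse events at other times, this will be logged". The same section has the external trials unit document and monitor serious events, and calls for a clinical assessment if suicidal ideation is expressed or worsening is suspected. It ties neither safeguard to a scheduled question.

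The timing follows from two other sections. Outcome measures: "The primary endpoint is 10 weeks after randomization". Waitlist: "Participants assigned to the waitlist will receive no in-home decluttering for a period of 10 weeks after group CBT", and then "After these 10 weeks (primary endpoint), participants on the waitlist will be crossed over and offered the same intervention as the active group".

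Ethics and dissemination describes the safety arrangements more broadly: "Adverse events will be carefully monitored throughout the trial". It gives no instrument or time point. It does say which harms are expected: short-term ones, with anxiety on discarding as the example.

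**The concern.** Everyone randomized is to be offered the same decluttering, but at different times. The only structured harms question in the text falls at the end of the first arm's course and before the second arm's course begins. The waitlist arm's checklist therefore describes a period without the intervention, and its later exposure is covered only by what happens to be reported.

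The trial will be read as evidence on whether home decluttering after group CBT is safe as well as effective. As written, systematic harms data under the intervention come from about half of those offered it, although the other half will be seen again at a scheduled follow-up. A reader of the Ethics section would expect more.

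**Working it through.** **Inputs**

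- Randomized: 90 (Participants: "We will randomize 90 participants to either in-home decluttering or a waitlist"), allocated 1:1 (Randomization), so 90 / 2 = 45 per arm.
- Checklist time: primary endpoint, week 10 (Recording and reporting of adverse events; Outcome measures).
- Waitlist exposure before week 10: none. Decluttering is offered afterwards (Waitlist).
- Contacts in weeks 1 to 10: 10 weekly home visits by social workers in the active arm (In-home decluttering), against 4 visits by a study assessor on the waitlist (Outcome measures; Discussion).
- Already randomized in May 2023: 48 (Trial status).

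The article gives no figure on this point to reproduce.

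**Step 1. Who is asked after exposure**

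| Arm | Checklist at week 10 covers | Checklist after own decluttering |
|---|---|---|
| Decluttering (about 45) | the decluttering period | yes, at week 10 |
| Waitlist (about 45) | the waiting period | none stated |

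So 45 / 90 = 50% of those to be offered the intervention are asked only before they have received it.

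**Step 2. What that costs in precision**

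If no event of a given type is seen among n people asked, the exact one-sided 95% upper bound on its rate is 1 − 0.05^(1/n).

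| n asked after exposure | Upper bound |
|---|---|
| 45 (as written) | 6.4% |
| 90 (full uptake and completion) | 3.3% |
| 38 (45 with 15% missing) | 7.6% |
| 76 (90 with 15% missing) | 3.9% |

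The 15% is the missing-data allowance in the sample size section, borrowed here as an assumption.

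The chance of seeing at least one event at true rate p is 1 − (1 − p)^n. For p = 2% it is 60% with n = 45 and 84% with n = 90. For p = 1% it is 36% and 60%. These rates are assumed for illustration.

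**Step 3. What can still be gained**

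Of the 48 randomized by May 2023, about 24 would be on the waitlist. If all 24 are past the 3-month visit when a change takes effect (an assumption), 45 − 24 = 21 waitlisted people remain. Then n = 45 + 21 = 66, and the bound is 1 − 0.05^(1/66) = 4.4%. A later change moves the bound back toward 6.4%.

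**Step 4. Whether the 3-month visit falls late enough**

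The crossed-over course lasts 10 weeks, and 3 months is about 13 weeks. The visit follows the course if it starts within about 3 weeks of the primary endpoint. The Blinding section itself expects every participant to have had, or been offered, decluttering by then.

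**The case against.** **The schedule figure is not available here.** The article does not use the word only. It refers to Fig. 2 for all measures and times, and to the full protocol for detail. The Fig. 2 legend lists both the checklist and the follow-up visits, so a checklist entry at follow-up cannot be excluded. This stands as a limit on the claim. It does not remove the point, because the text itself sets one structured time and a notification rule for the rest. If Fig. 2 says otherwise, that section is misstated and needs correcting.

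**The Ethics sentence can be read loosely.** Logging notified events, external monitoring of serious events and clinical assessment on suspicion are monitoring of a kind. That is fair, and these are real safeguards. They act only once someone has learned of an event, however, so they do not replace a scheduled question.

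**The cross-over phase is uncontrolled.** The Discussion says so. Harms data from it cannot improve the randomized contrast, but they do add to what is known about people exposed to the intervention.

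**Stronger readings that the article does not support**

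- A reader might infer that the waitlist arm is never asked about harms. It is asked once, at week 10, about the waiting period.
- A reader might infer that the between-arm harms comparison is biased. The week-10 checklist is given to both arms at the same time, and no section says that notified events are pooled with it.
- A reader might infer that notified events will be over-reported in the active arm because it has 10 visits against 4. Those visits are made by social workers, while the waitlist meets a study assessor directly, and the logging rule depends on the research team being told. Capture may well differ by arm, but the direction is not established.

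**Conclusion.** The point holds as a gap in coverage and a mismatch between two sections. On the article's text, about 45 of the 90 people offered decluttering have no structured harms question after receiving it, which is less than the Ethics section promises. The randomized week-10 checklist comparison and the efficacy analyses are not affected.

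The cost is the difference between a zero-event upper bound of 6.4% and one of 3.3%. The lower figure is the best case: it needs every waitlisted participant to take up the offer and complete the added checklist. With recruitment under way, the attainable bound lies between the two, before any allowance for missing checklists. The conclusion rests on an even 45/45 split and on Fig. 2 not already scheduling the checklist after cross-over. It is worth acting on because the remedy is small.

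**What to change.** 1. Give the SMURF checklist also at the existing 3-month follow-up, in both arms, with recall since the primary endpoint. Report harms from the cross-over phase as uncontrolled data.
2. Keep the between-arm harms comparison on the week-10 checklist. List notified events separately, by arm, because contact frequency and visiting staff differ.
3. Bring Recording and reporting of adverse events, Ethics and dissemination, and the Fig. 2 schedule into agreement on when the checklist is given.

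Do not add checklists at weeks 4 and 7 unless they can be elicited in the same way in both arms. Measures at those visits are collected by the treating social workers in one arm and by study assessors in the other, so an added checklist would bring in the arm difference that the week-10 comparison should avoid.

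The cost is a few minutes at a visit that already exists, plus a minor amendment. The added data are uncontrolled, and recall over about 3 months is longer than the 10 weeks covered at the primary endpoint, so brief events may be missed. Participants already past the 3-month visit will contribute nothing, and coverage will stay below 90.

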### Blinding

Assessors conducting primary endpoint assessments will be blind to group allocation. Participants will also be reminded by their assessors not to reveal their arm allocation. To measure blinding integrity, the primary endpoint assessments will be audio recorded. All assessors will guess each participant’s intervention allocation at each assessment point and motivate their choice. They will also register whether the participants inadvertently revealed their group allocation. If that is the case, the audio recording will be edited, and a new blind assessor will listen to the recording and conduct the rating that will be used in the trial. The follow-up assessments will not be blinded, because all participants will have received, or at least been offered, the in-home decluttering by the first follow-up assessment (3-month follow-up). The statistician performing data analyses will be kept blind to participant group allocation during the whole duration of the trial.

### Patient and public involvement

This trial builds upon previous feedback from therapists, social workers, patients, and patient organizations with a desire to improve collaboration between healthcare and municipalities.

The Task Force for Hoarding Disorder in Stockholm has been and will continue to be a collaborating partner in this study. This ensures that experience from every phase of the project is directly communicated to all relevant interested parties (including patient representatives). Moreover, patients will be represented by the Swedish OCD patient organization (https://ocdforbundet.se/), which is a member of the task force, making sure that the service user perspective is acknowledged throughout all phases of the project.

Individuals that have received treatment for HD outside the context of the current study have continuously had the opportunity to provide feedback about their experiences. As a result of this feedback, some small modifications to the CBT workbook in Swedish were made (e.g., simplifying and making worksheets easier to use and using the word “treatment” instead of “course”). The patient organization for OCD and related disorders in Stockholm (*OCD-föreningen Stockholms län*; in English: OCD Association in Stockholm County) provided feedback on the current design and some modifications to the exclusion criteria were made accordingly.

### Data management

Data will be collected manually and digitally and kept in case report forms (CRFs). Each participant will receive a trial identification number, and their data will be handled according to rules of confidentiality. The accuracy of the data entry for the primary outcome measures (self-reported SI-R and blind assessor-rated CIR) will be monitored by the Karolinska Trial Alliance, and a delegation log for staff involved in data handling will be used.

### Sample size calculation and statistical analysis

The power calculation in the current trial is based on individual-level data from a previous study of group CBT for HD with the SI-R as the primary outcome measure, rated at 3 time points [23]. A linear, 2-level mixed effects model (LMM) implemented using the R package powerlmm, version 0.4 (available at https://cran.r-project.org/src/contrib/Archive/powerlmm/) [43] was used to calculate the required sample size. In this model, the standard deviations of the random intercept (4.22), the random slope (2.54), and the residual error (5.68) were imputed. Given 80% power (two-sided alpha test), two groups (in-home decluttering and waitlist), and 4 SI-R observations (baseline, week 4, week 7, post-intervention) per participant, we estimated that a total of 80 participants would be needed to detect a slope difference between the two groups of 8 points on the SI-R at the primary endpoint. For the other primary outcome measure, the blind assessor-rated CIR, data from the same study was used. In that study, there were only data from two measurement points, and therefore, an ANCOVA was used to calculate power, adjusting for pre-treatment scores. Given 80% power (two-sided alpha test), two groups (in-home decluttering and waitlist), and 4 CIR observations (baseline, week 4, week 7, post-intervention) per participant, the estimate is that a total of 58 participants would be needed to detect a slope difference between the two groups of 1 point on the CIR at the primary endpoint.

To compensate for up to 15% missing data throughout the trial, we will recruit a total of 90 participants who will be randomized to one of two trial arms. However, due to the risk of dropouts before randomization, during or immediately after CBT, we plan to recruit patients to CBT until we have randomized 90 participants.

All data will be analyzed according to intention-to-treat principles with mixed effects models. The mixed effect regression model will include fixed effects of time, trial arm (intervention vs. waitlist), and an interaction effect of time by trial arm, as well as a random intercept to account for individual differences. Ordinal variables (such as the CGI-I and the CGI-S) will be analyzed with ordinal regression and binary data (e.g., remitter status) with logistic regression. The chi-square tests will be used to check whether the blinded assessor’s guesses on trial arm allocation are better than chance. The selected statistical model of mixed effect regressions can handle missing data, if more than 15% of data is missing an appropriate imputation method will be applied. Potential selection bias due to missing data will be assessed by comparing data from enrollment and baseline from participants with and without missing data on the primary outcomes using linear regression and by conducting sensitivity analysis. The statistician that will perform the data analyses will be independent from the research group and blind to group allocation.

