## Methods

### Study design and setting

This study is a parallel-group, superiority trial. All study participants will first undergo protocol-based group CBT [10] for 12 weeks, and within 10 days after the end of the CBT intervention, they will be randomly assigned (1:1 ratio) to either 10 weeks of in-home decluttering or a waitlist. Participants randomized to the waitlist will be offered in-home decluttering at 10 weeks post-randomization (i.e., after the primary endpoint). All participants will be followed up naturalistically 3, 6, and 12 months after the primary endpoint. Figure 1 shows a CONSORT flow diagram [11] of the study design. A SPIRIT checklist [12] can be found in the supplements.

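### The CIR sample size of 58 comes from a two-time-point, baseline-adjusted ANCOVA but is reported as power for a four-observation slope test, so the stated 80% is not the power of the planned analysis

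*Protocol article*

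**What the plan says.** All the relevant text is in the Protocol article, section Sample size calculation and statistical analysis.

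- Source of the CIR calculation: the earlier group-CBT study that also supplied the SI-R inputs. On its CIR data the article reports that "there were only data from two measurement points, and therefore, an ANCOVA was used to calculate power, adjusting for pre-treatment scores".
- Conditions attached to the result: "Given 80% power (two-sided alpha test), two groups (in-home decluttering and waitlist), and 4 CIR observations (baseline, week 4, week 7, post-intervention) per participant".
- The result: "a total of 58 participants would be needed to detect a slope difference between the two groups of 1 point on the CIR", evaluated at the primary endpoint.
- The planned analysis: "The mixed effect regression model will include fixed effects of time, trial arm (intervention vs. waitlist), and an interaction effect of time by trial arm". A random intercept is the only random effect listed, and no baseline covariate is named.

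The same section gives 80 participants for the SI-R and randomizes 90 to allow for up to 15% missing data. It prints no alpha level, no SD for the CIR and no correlation between baseline and endpoint CIR.

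**The concern.** The CIR power statement mixes two different calculations. An ANCOVA on pre and post values estimates a difference in endpoint means adjusted for baseline. It contains no slope, and data from two occasions cannot supply the covariance pattern of four visits. The four-observation slope wording fits the SI-R calculation just before it, which was done with a longitudinal mixed model. It does not fit the CIR calculation.

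The planned model differs again. Baseline is the first of the four outcome values and the arms may differ there, so the time-by-arm term compares change from baseline between arms. That is a legitimate estimator, but its variance is not that of the ANCOVA. At stake is whether the only power figure given for this primary outcome says anything about the test that will be run.

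**Working it through.** **Inputs.** From the article: 80% power, two-sided, 1:1 allocation, a 1-point difference, 58 in total (29 per arm), visits at baseline and weeks 4, 7 and 10, 90 randomized, 15% missing. Assumed because not printed: alpha 0.05, and a baseline-endpoint correlation rho from 0.3 to 0.9. Visits are taken as equally correlated, as a random-intercept model implies.

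**Step 1: the plan's own figure.** 58 cannot be reproduced forward without an SD, so I solve backwards. With n per arm = 2·SD²·(1.960 + 0.842)² / 1², setting n = 29 gives SD = √(29/2) / 2.802 = 1.36 (1.34 with a t-based calculation). This is the baseline-adjusted SD, σ√(1 − rho²), if 58 is a two-time-point ANCOVA. Nothing shows 58 to be wrong for that analysis.

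**Step 2: variance of the planned contrast relative to ANCOVA.**

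- ANCOVA at week 10: σ²(1 − rho²).
- Week-10 change contrast (time as categories): 2σ²(1 − rho). Ratio R = 2/(1 + rho).
- Linear slope over weeks 0, 4, 7, 10, expressed as the 10-week difference: 100·σ²(1 − rho)/54.75. Here 54.75 is the sum of squared deviations of the visit times from their mean of 5.25 (27.5625 + 1.5625 + 3.0625 + 22.5625). Ratio R = 1.827/(1 + rho).

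The article does not say how time is coded, so both forms are shown.

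**Step 3: sample size and power.** N per arm = 29·R, rounded up, then doubled. Power with n per arm = Φ(2.802·√(n/29)/√R − 1.960). Completers: 90 × 0.85 = 76.5, taken as 76 (38 per arm).

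| rho | N, change | N, slope | Power at 58, change / slope | Power at 76, change / slope | Power at 90, change / slope |
|---|---|---|---|---|---|
| 0.3 | 90 | 82 | 62% / 66% | 73% / 77% | 80% / 84% |
| 0.5 | 78 | 72 | 68% / 72% | 79% / 83% | 86% / 89% |
| 0.7 | 70 | 64 | 73% / 77% | 84% / 87% | 90% / 92% |
| 0.8 | 66 | 60 | 76% / 79% | 86% / 89% | 91% / 93% |
| 0.9 | 62 | 56 | 78% / 82% | 88% / 91% | 93% / 95% |

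Example, rho = 0.5, change contrast: R = 2/1.5 = 1.333; 29 × 1.333 = 38.7, so 39 per arm and 78 in total; power at 58 = Φ(2.802/1.155 − 1.960) = Φ(0.466) = 68%.

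**Step 4: the matching analysis.** If the CIR were analysed by the ANCOVA that produced 58, power would be 89% at 76 and 94% at 90.

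**The case against.** The strongest reply is that nothing follows for the trial. It never runs at 58: the SI-R requirement of 80 and the missing-data allowance set the size at 90. At 76 completers the less favourable form of the planned model still has 79-88% power for correlations of 0.5 to 0.9. This stands. A reader might infer that the CIR comparison is underpowered, but the documents do not support that unless the correlation is low (73-77% at 0.3).

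A second reply is that the direction of the error is not fixed. This also stands. With linear time and a correlation of 0.9 the planned model needs 56, slightly fewer than 58. It would be wrong to say flatly that 58 understates the need, or that 58 is a miscalculation.

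A third reply is that the planned model does handle baseline, because baseline is one of the repeated values and the interaction removes baseline differences. This is right. The model is standard and valid; what it lacks is a baseline covariate, and the consequence is a difference in efficiency, not bias.

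Two further inferences go too far. A reader might take the four-observation wording to mean an ANCOVA on the mean of three post-baseline visits. The planned model would then need far more participants (about 86 to 184 over the same correlations). But the article describes a calculation forced by having two measurement points and mentions no averaging over visits. A reader might also claim a definite power gain for the SI-R from baseline adjustment. Its size depends on a time scale that the article does not give and on a random slope that the analysis paragraph does not list, so no figure is offered.

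None of this repairs the text. The article specifies both the power method and the analysis model, and they disagree.

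**Conclusion.** The point holds as a mismatch between the CIR power statement and the planned analysis, and as a contradiction within the power statement itself. The printed 80% at 58 is not the power of the time-by-arm test. On the assumptions above, that test has 62-78% power at 58 as a week-10 change contrast, or 66-82% as a linear slope, and needs 62-90 or 56-82 participants.

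These ranges rest on alpha 0.05, on correlations of 0.3 to 0.9, on equal correlation between visits, and on reading 58 as a correct two-time-point ANCOVA result. The contradiction in wording needs none of these assumptions. No change to enrolment follows.

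**What to change.** 1. Restate the CIR figure as 58 for a week-10 ANCOVA adjusted for baseline, with two observations, and print the SD, the correlation and the alpha used.
2. Then make power and analysis agree, in one of two ways:
   - keep the planned model and restate CIR power for its time-by-arm contrast, naming the time coding; or
   - analyse the CIR with a mixed model of the post-baseline visits (weeks 4, 7 and 10) that adjusts for the baseline CIR.
3. Constrain the arms to a common baseline mean only if the baseline is taken before allocation is disclosed. The documents do not show this. Under Randomization, participants learn their allocation at the meeting before decluttering; under Outcome measures and the Fig. 2 legend, baseline falls before or during the first home visit. Under any of these models, an effect of allocation on the baseline itself would be partly or wholly removed from the estimate, so the plan should say when the baseline photographs are taken.

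The cost is a few sentences and, for the second route, a dated change to the CIR model made while the statistician is still blind. A baseline CIR is already scheduled, and no participants or visits are added.
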